### Statistical analysis

The statistical analysis will follow the intention-to-treat approach. A statistical analysis report will be written to describe all the findings according to the CONSORT statement recommendations [55].

The baseline characteristics of centres and patients will be described for each intervention group. Categorical variables will be described as numbers and percentages. Continuous variables will be reported using means and standard deviations or medians and interquartile ranges.

For the primary outcome, we will use generalized linear mixed modelling (Poisson mixed model) to provide statistical estimates controlling for each cluster, with the strategy intervention as a fixed effect and clusters as a random effect. The impact of the implementation order of intervention and control organization in the 2 periods on this outcome will be assessed. Additional sensitivity analysis could be performed with a permutation test.

Given the low rate of false positive rapid tests, any missing value (reactive rapid test not confirmed) will be considered as a success (positive test) in the analysis. Additional sensitivity analyses will also consider missing values as 1) success in the intervention group (HIV+ diagnosis confirmed) and failure in the control group (HIV- diagnosis confirmed); 2) failure in the intervention group and success in the control group.

The secondary outcomes regarding the presentation of patients newly diagnosed HIV positive for specialist consultation within 3 months and the rate of positive tests will be compared in the 2 groups using Pearson’s χ2 test or Fisher’s exact test when applicable. Any missing value for the rate of positive tests (reactive rapid test not confirmed) will be considered as a success (positive test).

Early diagnosis measured as the proportion of patients with CD4 counts >200/mm^3^ with no HIV-related symptoms will be compared between the 2 groups using Pearson’s χ2 test or Fisher’s exact test when applicable. The 2 other thresholds (>350/mm^3^, >500/mm^3^) with no HIV-related symptoms will also be explored. The missing values will not be replaced.

Results of the DICI-VIH questionnaires will be described.

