**Fig. 3 Fig3:**
[figure not shown]
DICI-VIH flow chart

EDs were identified before randomization. Eight EDs were selected and consented to participate (see Study settings). The randomization process assigned to each ED which strategy is to be applied in the first period (the alternative strategy being applied in the second period), with half of the clusters applying the control strategy in the first period, and the remaining half applying the intervention strategy (Fig. 2). The allocation schedule was computer generated. Both study periods are separated by a 4-week washout period. An equal number of participants had to be included in each centre for each period; thus the duration of the study periods vary per ED and per period.

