### Sample size

We assumed that the crossover design, which results in matched-pair data within each centre (increased statistical power of the comparison test), and the effect of the cluster study design (increased between-cluster variability decreasing the statistical power) cancel each other out, see [52] webappendix p1, [53].

The sample size calculation was performed with a comparison between 2 proportions with the hypothesis of superiority.

We hypothesize that, during the intervention period, the proportion of newly diagnosed HIV patients is similar to that found in non-targeted screening combined with current practice. Based on previous data [15], the proportion of new HIV diagnoses was expected at 1.04 and 3.38 per 10,000 patients, in the control strategy and in the intervention strategy respectively. Accordingly, a study sample of 140,000 patients which corresponds to the screening of 8,750 patients per centre and per period, would lead to a statistical power of 80 % with a 5 % two-sided type 1 error rate, using Fisher’s exact test (Pass v11.0.1 software [54]).

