There are some limitations to consider with the present study design. First, due to the consecutive inclusion periods in this cross-over study, there could be a risk of inter-period contamination in the centres that received the intervention first. The risk will be assessed during the analysis. However, this risk should be low as the periods are separated by a 4-week washout period and because providers are different in the 2 groups. Indeed, screening is offered by nurses during the intervention period whereas only physicians are involved during the control period. Second, in a trial requiring active patient and provider participation, the implementation of the 2 strategies will be associated with some variability between clusters regarding the proportion of new HIV diagnosis. This is not a default on the contrary; the cluster-randomized two-period crossover design is actually an asset for the estimation of between-cluster variability [58]. Moreover, assessing and understanding differences in intervention effectiveness and adherence from one ED to another is a core part of the analysis. In addition, the factors associated with screening refusal will be evaluated in the present study. They have already been explored in studies on non-targeted screening and results suggest that refusal is not associated with belonging to the highest risk groups [15, 59–61]. Third, the number of clusters (*n* = 8) is relatively small, with an associated limited statistical power of the test of interaction between intervention order and intervention effectiveness [62].

If the effectiveness of the intervention strategy is confirmed, the results of this trial could contribute to the development of recommendations and nurse-driven targeted HIV screening could be generalized in the French EDs of areas with high HIV prevalence. Finally, although the results may not be directly applicable to other countries, they could be helpful for decision makers in countries with concentrated epidemics.

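### The primary Poisson model for this two-period cluster crossover has no period term, so a time shift common to all EDs enters the strategy effect whenever the two sequence groups differ in diagnosis rate

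*Protocol article*

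**What the plan says.** The Study design section describes eight EDs, four per order, with two periods separated by a 4-week washout and equal patient numbers per ED and period; "thus the duration of the study periods vary per ED and per period". The primary analysis is a Poisson mixed model "with the strategy intervention as a fixed effect and clusters as a random effect". The next sentence adds: "The impact of the implementation order of intervention and control organization in the 2 periods on this outcome will be assessed". A permutation test is mentioned as an optional sensitivity analysis.

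The limitations in the Discussion mention a risk that arises "due to the consecutive inclusion periods in this cross-over study", but only as contamination between periods. They also expect some variability between clusters in new diagnoses, and concede limited power for the test of interaction between order and effectiveness.

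For planning, "the proportion of new HIV diagnoses was expected at 1.04 and 3.38 per 10,000 patients", with "a study sample of 140,000 patients which corresponds to the screening of 8,750 patients per centre and per period".

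**The concern.** Within each ED, strategy and time are tied together: one strategy is applied wholly before the other. If the underlying rate of new diagnoses, or of physician testing, moves between the periods, that movement counts for the intervention in control-first EDs and against it in intervention-first EDs. With four EDs in each order the two contributions offset exactly only if both groups carry the same total rate. The article describes no balancing of the groups beyond the 4/4 split.

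At stake is the within-ED contrast for which the crossover was chosen. Without a period term it keeps part of any common time shift, in a direction set by which EDs drew which order. The same contrast feeds the cost per extra diagnosis.

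**Working it through.** **The plan's own figure.** 8 × 2 × 8,750 = 140,000, or 70,000 per strategy. Exact enumeration of the two-sided Fisher test at 1.04 v 3.38 per 10,000 gives 81.2% power against the stated 80%. The sample size reproduces and is not affected by this point. Expected events are 70,000 × 1.04/10,000 = 7.28 and 70,000 × 3.38/10,000 = 23.66, about 31 in total, with a rate ratio of 3.25.

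**Distortion.** With equal patients per ED-period, the strategy rate ratio from a Poisson model with ED intercepts and no period term equals total intervention events over total control events. Let θ be the true ratio. Intervention events are proportional to θ(A + gB) and control events to gA + B, so the estimate targets θ × (A + gB)/(gA + B). Neither g nor A/B is given in the article; the values below are assumptions.

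| A/B | g = 0.7 | g = 0.8 | g = 1.2 | g = 1.5 |
|---|---|---|---|---|
| 1 | 1.000 | 1.000 | 1.000 | 1.000 |
| 1.5 | 1.073 | 1.045 | 0.964 | 0.923 |
| 2 | 1.125 | 1.077 | 0.941 | 0.875 |
| 2/3 | 0.932 | 0.957 | 1.037 | 1.083 |
| 1/2 | 0.889 | 0.929 | 1.063 | 1.143 |

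Example: A/B = 2, g = 1.5 gives (2 + 1.5)/(3 + 1) = 0.875, so 3.25 becomes 2.84. With A/B = 1/2 it becomes 3.25 × 1.143 = 3.71. Adding period to the fit on expected counts at A/B = 1/2, g = 1.5 returns 3.25.

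**Cost in precision.** Set A + B = 7.28 expected control-rate events in period 1. Without period, SE = √(1/I + 1/C), where I and C are the strategy totals. With period, SE = ½√(sum of 1/m) over the four order-by-period cells. For A/B = 2, g = 1.5 the cells are 15.77, 7.28, 2.43 and 11.83, so SE = ½√0.697 = 0.418. Mean squared error (MSE) is SE² plus squared log bias.

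| A/B | g | SE without | SE with | Change | MSE without | MSE with |
|---|---|---|---|---|---|---|
| 1 | 1.0 | 0.424 | 0.424 | 0% | 0.180 | 0.180 |
| 1 | 1.5 | 0.379 | 0.387 | +2% | 0.144 | 0.150 |
| 2 | 1.0 | 0.424 | 0.450 | +6% | 0.180 | 0.202 |
| 2 | 0.7 | 0.468 | 0.488 | +4% | 0.233 | 0.238 |
| 2 | 1.5 | 0.373 | 0.418 | +12% | 0.157 | 0.174 |
| 1/2 | 0.7 | 0.453 | 0.503 | +11% | 0.219 | 0.253 |
| 1/2 | 1.5 | 0.387 | 0.403 | +4% | 0.167 | 0.162 |

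**What the order check can see.** In a two-sequence crossover the order-by-strategy interaction is the same contrast as the period effect. At the planned event numbers with A = B and g = 1, its SE is also 0.424. For g = 1.5, log g/SE = 0.405/0.424 = 0.96, which gives about 16% power. Power of 80% needs log g = 2.80 × 0.424 = 1.19, that is g of about 3.3.

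**The case against.** The best defence is that omitting period is a reasonable trade of bias for variance. With about 31 events, the term costs more in variance than it saves in squared bias in most of the cells above. The bias is at most about a third of one standard error there (0.134 against 0.37–0.39). It averages to zero over random allocation. Order is randomised 4/4 with equal numbers per ED-period, and the article does promise to look at implementation order, with details that a full protocol or SAP may supply. All of this stands, and it limits the weight of the point. It does not settle it: the article states the primary model explicitly, attaches no consequence to the order assessment, and that assessment would miss shifts large enough to produce the distortions shown.

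Three stronger readings are tempting and not supported:

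- **The order was unstratified, or the second period falls in another season.** The article says only that the schedule was computer generated and that durations vary; it gives no period lengths.
- **The EDs are known to differ in diagnosis rate by some amount.** The rationale assumes differences in organisation and care practices, and the Discussion expects variability in new diagnoses, but neither gives a size.
- **The primary test is invalid.** In simulation without period, the two-sided type I error was 4.8% for a 2-fold group difference with g = 1.5. Among the reported cases it passed 5% only when the rate doubled between periods (7.2% and 10.9% for 2- and 3-fold group differences).

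**Conclusion.** The point holds as a recommended improvement to the stated primary model. A common period shift does not cancel from the strategy rate ratio unless the two groups of four EDs have equal total rates, and the article describes nothing that ensures this. The size is modest: about 4–14% on the rate ratio for an assumed 1.5- to 2-fold difference between groups at the tabulated values of g, against a standard error of about 0.4. Its direction cannot be known in advance. The case for the term is that the primary contrast should be free of a common time shift by design, and that fixing this now avoids a choice made after seeing the order assessment. It is not a claim that accuracy improves in every scenario.

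**What to change.** In the Statistical analysis section, specify the primary Poisson mixed model with strategy and period (first/second) as fixed effects and ED as random effect, and take the primary estimate from it. Report the model without period as a sensitivity analysis, and keep the order assessment as a secondary check.

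A two-level term removes only the shift common to all EDs. Because period lengths vary, calendar change that differs by ED would need calendar time in the model; add that as a sensitivity analysis.

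The cost is one model term and no new data. The standard error of the log rate ratio widens by about 0–12% over the ranges shown, and the mean squared error may be slightly larger at these event numbers.

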### Additional analyses

#### Factors associated with patient refusal of nurse-driven targeted HIV screening

In half the centres, all patients who have completed the DICI-VIH questionnaire, are at risk of HIV exposure and eligible for nurse-driven targeted HIV screening are considered over randomly selected 32-h observation periods of ED activity during 7 consecutive days. The patient characteristics reported in the DICI-VIH questionnaire, history of HIV testing and perceived HIV risk will be compared between patients refusing to be tested and patients accepting the rapid test in the context of nurse-driven targeted HIV screening. A descriptive analysis of these data will be performed.

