## Methods

### Study design

The DICI-VIH study is a multicentre (*n* = 8), cluster-randomized, two-period crossover trial.

The 2 strategies under comparison are:Current practice alone, consisting of physician-directed HIV diagnostic testing, which involves a medical interview and HIV test. This strategy is further referred to as the control strategy (Fig. 2).

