#### Secondary outcomes

The secondary outcomes are as follows:Proportion of patients newly diagnosed HIV positive who present for a specialist consultation within the 3 months following the test among those newly diagnosed HIV positive,Proportion of new HIV diagnoses among tests performed,How early diagnosis occurs in the course of the disease, defined as the proportion of patients that are newly diagnosed with CD4 counts >200/mm^3^ with no HIV-related symptoms, CD4 counts >350/mm^3^ with no HIV-related symptoms, and CD4 counts >500/mm^3^ with no HIV-related symptoms.

During the intervention period, the implementation of nurse-driven targeted HIV screening strategy is described by:The distribution rate of the DICI-VIH questionnaire: number of distributed questionnaires among included patients unaware of their HIV status and whose clinical presentation is compatible with the completion of the questionnaire,The completion rate of the DICI-VIH questionnaire: number of questionnaires completed among included patients unaware of their HIV status and whose clinical presentation is compatible with the completion of the questionnaire,The rate of patients found to be at risk: number of patients found to be at risk among included patients who filled the questionnaire,The test offering rate: number of patients who were offered a rapid test by nurses among patients found to be at risk,The acceptance rate: number of patients who accepted to be tested among patients who were offered a rapid test,The screening rate: number of rapid tests performed by nurses among patients found to be at risk,The rate of positive tests and rate of confirmed positive tests among rapid tests performed by nurses,The factors associated with patient refusal to be tested.

During this period, the acceptability of nurse-driven targeted HIV screening by providers and patient perceptions of the process are described qualitatively, as detailed in section 9.

The costs and cost-effectiveness of each strategy are also evaluated and are detailed in section 9.

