### Data collection and management

During both periods, general data of patient flow are collected on a daily basis in each centre by the research team on a paper CRF, including:Total number of patients,Number of patients aged 18 to 64 not presenting secondary to HIV exposure,Number of patients aged 18 to 64 not presenting secondary to HIV exposure who are tested for HIV (either rapid test or Standard enzyme linked immunosorbent assay) as ordered by a physician,Number of patients whose HIV diagnosis is confirmed to be positive by serology,Number of patients newly diagnosed HIV positive presenting for a specialist consultation and their characteristics (CD4 counts, viral load, HIV, HBV, HCV and Syphilis serological status and their clinical presentation). These data are downloaded with the help of the laboratory personnel in each hospital and the infectious disease specialist.

Additionally, during the nurse-driven targeted HIV period, data are also recorded by the research team on a paper CRF:Number of patients aged 18 to 64 not presenting secondary to HIV exposure, unaware of their HIV status and whose clinical presentation is compatible with the completion of the questionnaire,Number of patients who were distributed the DICI-VIH questionnaire and who filled it out,Number of patients found to be at risk,Number of patients found to be at risk and who were offered a rapid test by a nurse,Number of patients found to be at risk and tested by a nurse,Number of patients tested with a reactive rapid test (confirmed or not confirmed positive by serology),Number of patients whose HIV diagnosis is confirmed to be positive by serology.

With the help of the research team, nurses collect individual data from the DICI-VIH questionnaire (patient risk assessment on the patient page (Fig. 1) and offering rate, acceptance rate and screening rate on the nurse page) on an e-CRF. The quality of these data is controlled on site by the monitoring team.

Upon study completion, ED flow data, including patient baseline characteristics, degree of severity and time spent in the ED will be extracted from the electronic patient-level ED database.

A data manager collects all study data on a secure password-protected server. A quality team, independent from the coordination team, will perform an internal audit of data completeness and will ensure the individual data matches the data collected on the e-CRF.

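### The refusal comparison is confined to short windows in half the EDs, although the risk answers and acceptance it needs are recorded individually in all eight

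*Protocol article*

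**What the plan says.** Under Secondary outcomes, the protocol article lists "The factors associated with patient refusal to be tested" among the intervention-period measures, with no restriction to a subsample. The Secondary objectives section is equally unrestricted.

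The method appears only under Additional analyses, in the section on factors associated with refusal. The population begins "In half the centres, all patients who have completed the DICI-VIH questionnaire, are at risk of HIV exposure", and these patients "are considered over randomly selected 32-h observation periods of ED activity during 7 consecutive days". Refusers and accepters are to be compared on three groups of variables: questionnaire characteristics, HIV testing history and perceived HIV risk. The analysis is descriptive.

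Data collection and management has nurses enter individual questionnaire data: the risk assessment from the patient page, and "offering rate, acceptance rate and screening rate on the nurse page) on an e-CRF". No limit by ED or by time is set. Study procedures describes support for eCRF data collection in each participating ED.

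**The concern.** For one of the three groups of variables, the questionnaire characteristics, the stated analysis population is much narrower than the data. Both sides of the comparison, the risk answers and the accept-or-refuse outcome, are held per patient across the trial's intervention periods. The written plan uses them only in a few observation periods in four EDs.

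Two things are lost. The first is precision: few refusers will fall in the windows, so differences in refusal between risk groups will be estimated loosely. The second is coverage: four EDs contribute nothing to the comparison, although the Discussion treats variation in effectiveness and adherence between EDs as central to the analysis and says refusal factors will be evaluated.

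The other places that use these data do not fill the gap. Statistical analysis promises a description of questionnaire results, and Secondary outcomes an overall acceptance rate. Neither compares refusers with accepters.

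**Working it through.** **Inputs from the article.** Eight EDs ("The DICI-VIH study is a multicentre (*n* = 8), cluster-randomized, two-period crossover trial") and "a study sample of 140,000 patients which corresponds to the screening of 8,750 patients per centre and per period". Check: 8 × 2 × 8,750 = 140,000, so the intervention periods hold 8 × 8,750 = 70,000 patients. The article gives no sample size or data share for the refusal analysis, so there is no stated figure to reproduce on that point.

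**Inputs that must be assumed.** The article gives neither period length nor daily ED volume; Study design says only that durations vary. Let d be eligible patients per ED per day, taken from 40 to 250. The plural wording leaves open whether an ED contributes one 32-h period or several. Seven days hold 168 h, so at most five such periods (160 h) fit.

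**Share left out.** With h observed hours per ED and H = 24 × 8,750/d hours in the intervention period:

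share left out = 1 − (4/8) × h/H

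Completion and at-risk rates cancel if they are constant over time and across EDs. Example at d = 100: H = 24 × 87.5 = 2,100 h, and 1 − 0.5 × 32/2,100 = 99.2%.

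| d per day | Period, days | One period (32 h) | Two (64 h) | Five (160 h) |
|---|---|---|---|---|
| 40 | 218.8 | 99.7% | 99.4% | 98.5% |
| 60 | 145.8 | 99.5% | 99.1% | 97.7% |
| 100 | 87.5 | 99.2% | 98.5% | 96.2% |
| 150 | 58.3 | 98.9% | 97.7% | 94.3% |
| 250 | 35.0 | 98.1% | 96.2% | 90.5% |

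The range is about 90% to 99.7%. With one 32-h period, 99% is exceeded only if 0.5 × 32/H < 0.01. That requires H > 1,600 h, a period longer than 66.7 days (d below about 131).

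**Patient numbers.** Assume 8% to 18% at risk (8% is the share meeting the main targeting criteria in Study settings; 18% is the questionnaire pilot) and 30% to 96% completion (96% is the pilot response rate; 30% is an assumed low value).

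- All EDs, whole intervention period: 70,000 × 0.08 × 0.30 = 1,680, up to 70,000 × 0.18 × 0.96 = 12,096 at-risk completers.
- One 32-h period in four EDs: 4 × d × 32/24 × at-risk share × completion. At d = 60 with the low rates this is 7.7; at d = 150 with the high rates it is 138.

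Both counts shrink further where no test is offered.

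**What this does to precision.** As an illustration, assume 25% refusal and a factor that splits patients evenly. The 95% half-width for a difference in refusal, ignoring clustering, is 1.96 × √(2 × 0.25 × 0.75/(n/2)) = 1.96 × √(0.75/n).

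- n = 138: about 14 percentage points.
- n = 5 × 138 = 691 (five periods): about 6.5 points.
- n = 1,680: about 4 points.
- n = 12,096: about 1.5 points.

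At n near 8 the approximation is not usable. Whatever the refusal rate, the interval widens by 1/√(share used): about 3 times at 9.5% used (1/√0.095 = 3.2) and about 18 times at 0.3% used (1/√0.003 = 18).

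**The case against.** The strongest reply is that the sub-study has a purpose of its own. Testing history and perceived risk are not among the questionnaire contents described in the article or the routine data items, so they apparently need extra collection, and sampling windows is a sensible way to do that. This stands: for those two variables no recorded data are left unused.

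A second reply is that nothing says the e-CRF data will be excluded from a refusal comparison, and that a condensed article may leave such a tabulation to the analysis plan. It is right that exclusion is not stated, and a reader should not infer that the sponsor has decided to discard those records. But the article is not silent on the population. It names one for this comparison, includes the questionnaire characteristics in it, and describes no wider one.

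Third, the aim is descriptive, with no test or power claim, and a small sample can serve a descriptive aim. That is fair. A reader might infer from the small windows that the refusal question cannot be answered at all; the article does not support that. The loss is in precision and coverage.

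Finally, a regression on the risk items has a difficulty. At least one positive risk answer is what makes a patient at risk (Intervention strategy section), so selecting on these items induces associations among them. Mutually adjusted coefficients then need care, and the fix should say so.

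**Conclusion.** The point holds for the questionnaire variables only. The stated comparison of refusers and accepters leaves out half the EDs and the large majority of the individually recorded data, about 90% to 99.7%. That range rests on an assumed 40 to 250 eligible patients per ED per day, one to five 32-h periods per ED, and constant completion and at-risk rates.

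A reader might go further and say that over 99% is left out. That needs both a single 32-h period per ED and an intervention period longer than about 67 days, or more restrictive assumptions still if several periods are observed. The article fixes neither, so the figure should not be stated as fact.

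The consequence is a listed secondary outcome described less precisely, and in fewer EDs, than the trial's own data allow. This is a minor, worthwhile improvement to a descriptive secondary analysis; the primary comparison does not depend on it.

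**What to change.** For the questionnaire variables, define the refusal comparison on all at-risk patients offered a rapid test, in all eight EDs over the whole intervention period, using the e-CRF. Account for ED, either by tabulating refusal by risk item within each ED or with a regression that includes ED. State that the risk items also define who is at risk, so that mutually adjusted associations among them are read cautiously; unadjusted refusal proportions for each item should be shown alongside.

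Keep the 32-h sub-study for HIV testing history and perceived risk, and state whether each ED contributes one 32-h period or several.

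The cost is one small extra analysis of data already being collected, plus a sentence or two of text.
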